### Recruitment procedure

The recruitment and data collection will be conducted from October 2019 to March 2021. Eligible patients will be approached and informed about the IMPPETUS study by the study staff to determine whether they would be willing to participate in the study, especially giving the consent to be willing to participate at a time point 6 months after intervention (t_2_). If the patients give their consent, a screening with the ‘Global Assessment of Functioning’ (GAF) and the ‘Health of the Nation Outcome Scales’ (HoNOS) will be carried out to identify patients with severe mental illness according to the definition above. The screening will be conducted as soon as possible after admission. For more details *see* Fig. 1.

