Changes in service use (*see* objective 3) will be measured as changes on the German version of the ‘Client Sociodemographic and Service Receipt Inventory’ (CSSRI) [14]. The CSSRI is a semi-structured interview to assess social and demographic data, accommodation data, detailed information regarding treatment, professional visits and social and health service utilisation for estimating healthcare costs. Additionally, the CSSRI systematically records the use of psychiatric, medical, psychosocial and rehabilitative health services (direct costs) and productivity losses (indirect costs) and therefore completely covers the costs of the disease from an economic perspective. Therefore, the health economic evaluation (see objective 6) will be based on the data collected with the CSSRI. An appropriate pre-structuring of the requested health care services will ensure that the receipt of the psychosocial care services recommended in the S3 guideline ‘Psychosocial interventions’ will be assessed.Satisfaction with treatment (*see* objective 4) of the patients will be assessed with the German satisfaction questionnaire ‘ZUF-8’ [15]. The ZUF-8 has eight items and is a one-dimensional measure of satisfaction to record the general or overall patient satisfaction with the treatment received. The item values are summed. High scale values indicate a large level of satisfaction and low scale values a low ‘satisfaction‘ (range from 8 to 32).Changes in patient treatment needs and coverage of needs (*see* objective 5) will be assessed by using the German version of the ‘Camberwell Assessment of Need’ (CAN-EU) [16, 17]. The CAN-EU assesses 22 domains of potential individual care needs. Each domain is rated on a 3-point scale from the absence of need (= 0) to the presence of an unmet need (= 2). A total score is calculated by adding the domain ratings.Quality of Life (QoL; *see* objective 6) of the patients will be measured with the German version of the World Health Organization’s Quality of Life Instrument-abbreviated version (WHOQOL-BREF) [18, 19]. The WHOQOL-BREF is a tool with 26 items: 24 items in four domains: physical (seven items), psychological (six items), social (three items) and environmental (eight items), and two additional items: the overall quality of life (item 1) and level of satisfaction with health (item 2). The items are rated on a five-point Likert-type scale. To calculate domain scores, the mean of all items within a domain is multiplied by four. Subsequently, these raw domain scores are transformed into a scale from 0 to 100 points (to enable comparisons to be made between domains composed of unequal numbers of items), with higher scores denoting better QOL.The calculation of quality-adjusted life years (QALYs; *see* objective 7) will be based on the German Version of the EuroQol (EQ-5D-5 L) [20–22]. The EQ-5D-5 L generates health states at five dimensions as a basis for the generation of QALYs. The EQ-5D-5 L questionnaire includes five questions on current issues in the dimensions of ‘mobility‘, ‘self-care‘, ‘usual activities‘, ‘pain/discomfort‘ and ‘anxiety/depression‘. Five possible answers exist for each dimension: (1) no problems, (2) slight problems, (3) moderate problems, (4) severe problems and (5) unable to do. QALYs will be generated by means of the German value set [23].In addition, the participation and social inclusion of the patients will be assessed using the German questionnaire ‘Fragebogen zur Erfassung sozialer Partizipation und sozialer Inklusion chronisch psychisch erkrankter Menschen’ (F-INK) [24]. The F-INK measures the participation and social inclusion of individuals with a chronic mental disorder. It is a modular questionnaire with nine modules that assess the central dimensions of social inclusion [24].Sociodemographic data of the patients (e.g., sex, age and socioeconomic data) and patient medical history will be assessed within the CSSRI. The patient’s medical history (diagnosis, length of illness, length of current disease episode, number of previous episodes and current somatic and psychotherapeutic treatment) will be derived from the patient or the patient’s record data.

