### Data collection and management

Patients and relatives will be interviewed by the study staff at three time points: shortly after admission (baseline, t_0_), 2 weeks after visiting both parts of the group sessions (intervention group) or 6 weeks after t_0_ (control group) (t_1_), and 6 months after t_0_ (t_2,_ both groups) (*see* Table 1). Due to the large number of outcomes to be measured, the interview can, if necessary, be divided into several appointments in order to avoid excessive demands on the participants. The collected data will be recorded on paper and subsequently entered in a standardized data form at the recruiting centres. Data entry will be done by one study member and checked by another member (double check) to avoid mistakes. Data will be stored in a secured computerised database centrally at the study centre Günzburg. Participant files will be maintained in storage for a period of 10 years after completion of the study.

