All other outcomes (*see* chapter ‘Outcomes and measurement’) will be analysed in a similar way. Subgroup analyses will be conducted separated by recruiting centres. Patient-related analyses (knowledge, attitudes, and experiences, service use, satisfaction with treatment, treatment needs and quality of life) will be conducted separately for patients with F2x and F3x diagnoses in additional subgroup analyses. Other categorisations based on quantitative variable are not planned.

Health economic evaluation (HEA) will be conducted from the societal and from the payer (statutory health insurance) perspective. Incremental cost-utility ratios (ICUR) will be computed using the differences in total (direct and indirect) costs of illness and the differences in quality-adjusted life years (QALY) between study groups over 12 months for the societal perspective. For the HEA from the payer perspective only the direct costs reimbursed by the statutory health insurance will be used as ICUR numerator. For both perspectives the stochastic uncertainty of the ICUR will be estimated by means of nonparametric bootstrapping with 2000 replications [34]. Probability of cost-effectiveness at MWTP for the gain of one QALY in the range between 0 and 100,000 € will be estimated for both perspectives by means of the cost-effectiveness acceptability curve [34]. The calculation of the QALY is based on the EQ-5D-5 L by means of the German value set [23].

All analyses will be conducted separately for patients and relatives.

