## Abbreviations

BAS: Burden Assessment scale
CAN-EU: Camberwell Assessment of Need
CSSRI: Client Sociodemographic and Service Receipt Inventory
DE: Design effect
DGPPN: German Association for Psychiatry, Psychotherapy and Psychosomatics
EPAS: Empowerment in the Process of Psychiatric Treatment of Patients with Affective and Schizophrenia Disorders Scale
EQ-5D-5 L: EuroQol
FCS: Fully conditional specification
F-INK: Questionnaire to Assess the Participation and Social Inclusion of the Patients
GAF: Global Assessment of Functioning
HEA: Health Economic Evaluation
HoNOS: Health of the Nation Outcome Scales
ICC: Intra-cluster correlation coefficient
ICUR: Incremental cost-utility ratios
IMPPETUS: Implementation of the Patient Version of the Evidence-based Guideline for Psychosocial Interventions for Patients with Severe Mental Illness
modITT: Modified intention-to-treat
MWTP: Maximum willingness to pay
QALY: Quality-adjusted life year
S3 guideline: Evidence and consensus-based guideline
SD: Standard deviation
t_0_: Assessment shortly after admission (baseline)
t_1_: Assessment 2 weeks after visiting both parts of the group sessions (intervention group) or 6 weeks after t_0_ (control group)
t_2_: Assessment 6 months after t_0_
TAU: Treatment as usual
WHOQOL-BREF: World Health Organization’s Quality of Life Instrument-abbreviated version
ZUF-8: German satisfaction questionnaire

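### The cost-utility comparison is set over 12 months, but the last interview is 6 months after baseline and nothing in the article bridges the gap

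*Protocol article*

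**What the plan says.** Under Statistical methods, the health economic evaluation computes ICURs from differences in total costs and "the differences in quality-adjusted life years (QALY) between study groups over 12 months for the societal perspective". For the payer perspective the section changes only which costs enter the numerator and names no horizon of its own. Bootstrapping and acceptability curves follow for both perspectives.

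On costs, Other outcomes says that "the health economic evaluation (see objective 6) will be based on the data collected with the CSSRI". QALYs come from the EQ-5D-5L with the German value set.

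On timing, Data collection and management says: "Patients and relatives will be interviewed by the study staff at three time points: shortly after admission (baseline, t_0". The second interview, t1, follows some weeks later. The third is placed "6 months after t_0_ (t_2,_ both groups". The abbreviation list agrees: "t_2_: Assessment 6 months after t_0". The Recruitment procedure section uses a different anchor, asking for patients "willing to participate at a time point 6 months after intervention (t_2".

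**The concern.** The analysis horizon is twice as long as the follow-up. Costs and utilities for months 7 to 12 are not collected, and the article does not say how they would be supplied.

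If the sentence were followed literally, the result would depend on an assumption about persistence that could be chosen after the data are seen. The bootstrap would not show this uncertainty, because resampling patients reflects only what was measured on them. Cost-utility is a listed objective and is announced in the abstract, so the horizon needs to be one that the trial can support.

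**Working it through.** **Inputs**

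- Stated horizon: 12 months (Statistical methods).
- Last interview: t2, 6 months after t0 (Data collection and management; Abbreviations). The primary outcome and the 70% retention assumption in Sample size also refer to 6 months.
- Utility difference between arms: not given. Assumed constant at d = 0.02, 0.05 or 0.10, for illustration only.

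**Step 1: horizon against schedule.** Observed span = t2 − t0 = 6 months. Shortfall = 12 − 6 = 6 months, or 6/12 = 50% of the stated horizon. The stated figure is not reproduced from the schedule.

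**Step 2: does the other anchor for t2 help?** If t2 is 6 months after the intervention, it would reach 12 months from t0 only if the intervention ended 12 − 6 = 6 months after t0. The schedule does not suggest this. In the intervention arm t1 comes 2 weeks after both group sessions, and in the control arm it comes 6 weeks after t0. If the two were meant to match, the sessions would end about 6 − 2 = 4 weeks after t0 (an inference), which puts t2 near 7 months.

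**Step 3: effect on the QALY difference.** With a constant difference d, the gain over 6 months is d × 0.5. Over 12 months it is d × 0.5 if the difference vanishes after t2, and d × 0.5 + d × 0.5 = d if it persists in full.

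| d (assumed) | Observed, 6 months | 12 months, no persistence | 12 months, full persistence |
|---|---|---|---|
| 0.02 | 0.010 | 0.010 | 0.020 |
| 0.05 | 0.025 | 0.025 | 0.050 |
| 0.10 | 0.050 | 0.050 | 0.100 |

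**Step 4: effect on the ICUR.** ICUR = ΔC / ΔQALY. With ΔC held fixed, the ratio of the two extremes is d / (0.5 × d) = 2, whatever d is. In practice ΔC would change with the horizon too, and not necessarily in proportion, since t0 falls shortly after a hospital admission.

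**Step 5: calendar, as weak support only.** Recruitment procedure states: "The recruitment and data collection will be conducted from October 2019 to March 2021". Trial status gives first enrolment as 28 October 2019 and end of recruitment as 31 March 2021, a span of 520 days. A 12-month follow-up ending by 31 March 2021 would fit only patients enrolled by 31 March 2020, which is 155/520 = 30% of that span. A 6-month follow-up would not fit everyone either: enrolment by 30 September 2020 gives 338/520 = 65%. The calendar therefore does not settle the horizon. The visit schedule does.

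**The case against.** **A 12-month visit might appear in Table 1, which is not shown.** This is unlikely. The text lists all three interview times in words and refers to that table for them.

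**The 12 months might combine a look-back at baseline with 6 months of follow-up.** The CSSRI recall period is not stated, so this cannot be ruled out for costs. It would add only costs incurred before the intervention. It cannot supply QALYs, because the EQ-5D-5L is described as asking about current problems. Costs and QALYs would then cover different windows.

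**An extrapolation method could sit in the full protocol or a health economic analysis plan.** That is fair as far as the method goes, and its absence from a condensed article is not the point. What stands is that the article states a horizon that its own schedule does not cover. A drafting slip is quite possible, in which case the analysis would simply run over 6 months.

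**Stronger readings the documents do not support:**

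- A reader might infer that no cost-utility analysis is possible. A 6-month ICUR can be computed from the planned data, and a 12-month one can be computed with extrapolation.
- A reader might take it as given that the EQ-5D-5L and CSSRI are collected at t0, t1 and t2. The visible text does not assign instruments to visits.
- A reader might say that both perspectives are explicitly fixed at 12 months. The wording attaches this to the societal perspective. That it carries over to the payer perspective is a reasonable inference, since only the numerator changes there, but it is not stated.

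**Conclusion.** The contradiction holds. The article specifies a 12-month comparison while its last interview is 6 months after t0, so half of the stated horizon is unobserved and a 12-month ICUR cannot be obtained from observed trial data. At fixed incremental cost, the choice between no persistence and full persistence after t2 moves the ICUR by up to a factor of 2. That figure assumes a constant utility difference up to t2 and is illustrative.

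The point is confined to the health economic evaluation, a secondary objective. A reader might infer that it weakens the trial's main result. It does not, because the confirmatory EPAS analysis uses the 6-month assessment and does not depend on the economic horizon. The correction should be made before the economic analysis starts, but it is not a defect in the primary analysis.

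**What to change.** 1. In Statistical methods, replace the 12-month horizon with t0–t2 (6 months) and state it for both the societal and the payer perspective.
2. Compute costs and QALYs over that same window. Take QALYs as the area under the EQ-5D-5L utility curve, using whichever interviews collect the EQ-5D-5L and CSSRI and the actual assessment dates.
3. If a 12-month figure is wanted, report it only as a prespecified extrapolation scenario, labelled as such, with its persistence assumption stated and varied.
4. Reconcile the definition of t2 in Recruitment procedure (counted from the intervention) with that in Data collection and management and in Abbreviations (counted from t0), since this fixes the length of the window.

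This is a change of wording and needs no new data. The price is a shorter horizon, which leaves any later costs or benefits unmeasured. Adding a 12-month EQ-5D-5L and CSSRI assessment would also resolve the conflict, but it would mean a further round of data collection.

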### Interventions

In centres randomised to the experimental group, the patient guideline ‘psychosocial interventions in severe mental disorders’ will be implemented using a multimodal strategy. The core component will be a two-part group session for patients of more than 60-min duration in which the contents of the patient guideline will be clearly presented (e.g., with case examples). The group session will be carried out jointly by the study staff (e.g., a psychologist) and a peer tutor (person with a lived experience of mental illness). The group sessions will also pay attention to the availability of psychosocial interventions in the regions but will not be limited to regional offers. In addition, questionnaires and decision aids on the basis of the patient guideline will be developed to assist patients in their discussions with practitioners and to promote their active demand for suitable psychosocial therapies. Training for the use of the questionnaires and decision aids will be provided in group sessions. Individual reminders will be developed. The two-part group sessions will be offered weekly in the inpatient and day hospital setting. Participation in both parts of the event will be supported by written information flyers. Repeated participation is possible, but study participants should attend both parts at least once. Furthermore, participants will receive the patient guideline as a printed book. Essential contents of the patient guideline will be made available on the Internet and will be optimized for mobile use (www.thera-part.de). The group sessions will include a brief introduction on how to use ‘TheraPart’. The plain language materials will be developed or tested with the participation of representatives of patients and relatives. A on-part information event for relatives will occur parallel to the two-part group events for the patients.

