### Sample size

Sample size calculation was based on a two-step procedure due to the hierarchical data structure. In the first step, the sample size for an individual randomized study is calculated. Based on studies using the ‘empowerment in the process of psychiatric treatment of patients with affective and schizophrenia disorders (EPAS)’ scale [26], a medium effect (0.4 SD units) of the implementation intervention on the primary endpoint is expected. This effect is detectable with an error probability of 5% (alpha) and a power of 80% by a t-test for independent samples with a sample size of 2 × 100 participants (200 in total).

The second step takes the cluster structure of the data into account. We assume that each centre recruits 35 patients (m) on average. The design effect (DE) is needed for the inflation of the group sample size: DE = 1 + (m - 1) * ICC with the fixed cluster size m and the intra-cluster correlation coefficient ICC. We assume a liberal intra-class correlation coefficient of 0.02 to control for the correlation of the outcome of participants of the same centre. Thereby, the DE is 1 + (35–1) * 0.02 = 1.68, which gives a sample size of 200 × 1.68 = 336 patients. As every centre recruits 35 patients on average, 10 centres are needed for the trial. Due to the severity of the disease in the patient population, case number planning assumes that 70% of patients can be reached 6 months after t_0_, so that an oversampling to (35/0.7) 50 patients per study centre will be recruited, resulting in 10 centres * 50 patients = 500 participants (2 × 250) as the overall sample size. This 70% estimate is based on experiences at the Günzburg site from three studies conducted with similar populations [27–29].

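### As written, the societal cost-utility numerator does not capture the cost of delivering the intervention, and the bootstrap is not said to respect randomisation by centre

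*Protocol article*

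**What the plan says.** All references are to the protocol article.

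- **Societal numerator** (Statistical methods): incremental cost-utility ratios are "computed using the differences in total (direct and indirect) costs of illness and the differences in quality-adjusted life years (QALY) between study groups over 12" (the horizon, in months, is a separate matter, and nothing here rests on it).
- **Payer numerator** (Statistical methods): "only the direct costs reimbursed by the statutory health insurance will be used as ICUR numerator".
- **Source of cost data** (Other outcomes): "the health economic evaluation (see objective 6) will be based on the data collected with the CSSRI". The section describes the CSSRI as recording health services used, as direct costs, and lost productivity, as indirect costs.
- **What is delivered** (Interventions): "The group session will be carried out jointly by the study staff (e.g., a psychologist) and a peer tutor". Sessions are offered weekly. Participants also receive the guideline as a book, and there are decision aids, questionnaires, individual reminders and a mobile website. Control patients get usual treatment and the same flyer that the intervention group receives.
- **Uncertainty** (Statistical methods): "the stochastic uncertainty of the ICUR will be estimated by means of nonparametric bootstrapping with 2000 replications". The acceptability curve for thresholds from 0 to 100,000 € is planned for both perspectives. The unit of resampling is not named.
- **Clustering** (Sample size, Randomisation): ten centres are randomised 1:1, and the sample size carries a design effect for correlation within centres.

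**The concern.** The trial tests a way of implementing a guideline, so the resource that separates the arms is the implementation itself. The article gives the societal numerator a definition and a data source, and delivery cost fits neither as they are worded. An analyst who follows the text would attach no price to the sessions and materials. The acceptability curve would then answer the cost-per-QALY objective for a programme treated as free.

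The second issue is precision. Centres are randomised, so cost and QALY differences between arms carry between-centre variation. The article allows for this in the sample size and in the primary model, but the economic paragraph does not say that it is carried into the bootstrap. If it were not, the curve would look more certain than the data justify.

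**Working it through.** **1. What the numerator contains**

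| Resource | In CSSRI-based cost of illness, as described? | Arm that uses it |
|---|---|---|
| Services used, lost productivity | Yes | Both |
| Flyer | Not named | Both, so it cancels |
| Session time of study staff and peer tutor | Not named | Experimental |
| Printed book, decision aids, reminders | Not named | Experimental |
| Website | Not named | Introduced in experimental sessions |

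The CSSRI is to be pre-structured so that services recommended in the guideline are captured. The implementation sessions tell patients about those services and are not evidently among them.

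**2. Direction**

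Net benefit at threshold λ is λ × ΔQALY − ΔCost. If a delivery cost of c per experimental patient is missing from ΔCost, the computed net benefit is too high by c at every λ, whatever the sign of ΔQALY. The ratio itself falls by c / ΔQALY, and this reads as more favourable only when ΔQALY is positive.

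**3. Size of the cost effect**

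The documents state no delivery cost, QALY gain or ICUR. The figures below are assumptions that only show how strongly the shift c / ΔQALY depends on its inputs:

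| Assumed c per patient | ΔQALY 0.005 | ΔQALY 0.02 | ΔQALY 0.05 |
|---|---|---|---|
| EUR 50 | 10,000 | 2,500 | 1,000 |
| EUR 100 | 20,000 | 5,000 | 2,000 |
| EUR 400 | 80,000 | 20,000 | 8,000 |

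The shift runs from EUR 1,000 to EUR 80,000 per QALY. It could be trivial or decisive on a 0 to 100,000 € scale.

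**4. The article's own clustering figures**

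For an effect of 0.4 SD, two-sided 5% alpha and 80% power, the t-test needs 99.1 per arm, so 100. The article then states: "We assume a liberal intra-class correlation coefficient of 0.02 to control for the correlation of the outcome of participants of the same centre". The design effect is 1 + (35 − 1) × 0.02 = 1.68, and 200 × 1.68 = 336. Then 336 / 35 = 9.6, so 10 centres; 35 / 0.7 = 50 per centre; 10 × 50 = 500. All of the stated figures reproduce.

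**5. What patient-level resampling would do**

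This step assumes that patients are resampled as independent, m = 35, normality, and an ICC for net benefit that the documents do not give. The true SE divided by the bootstrap SE is √(1 + 34 × ICC). Coverage of a nominal 95% interval is 2Φ(1.96 / ratio) − 1. An acceptability probability p becomes Φ(Φ⁻¹(p) / ratio).

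| ICC | SE ratio | Coverage | p = 0.95 becomes |
|---|---|---|---|
| 0 | 1.00 | 95% | 0.95 |
| 0.01 | 1.16 | 91% | 0.92 |
| 0.02 (EPAS value) | √1.68 = 1.30 | 87% | 0.90 |
| 0.05 | 1.64 | 77% | 0.84 |
| 0.10 | 2.10 | 65% | 0.78 |

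**6. Would resampling whole centres be enough?**

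A simulation used 5 against 5 centres of 35 patients, a normal outcome, 400 trials and 1,000 resamples each.

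| ICC | Empirical SE | Patient bootstrap: SE, coverage | Simple centre bootstrap: SE, coverage |
|---|---|---|---|
| 0.02 | 0.132 | 0.107, 0.89 | 0.116, 0.88 |
| 0.05 | 0.181 | 0.106, 0.74 | 0.150, 0.87 |
| 0.10 | 0.223 | 0.105, 0.63 | 0.192, 0.87 |

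With 400 trials, a coverage of 0.88 has a Monte Carlo error of √(0.88 × 0.12 / 400) = 0.016, so the two methods cannot be told apart at ICC 0.02. The simple centre bootstrap falls short because resampling k centres per arm understates the between-centre variance by (k − 1) / k = 4/5, an SE factor of √0.8 = 0.89.

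**The case against.** **Delivery costs are nowhere said to be excluded.** This is true, and a reader who infers a decision to price the intervention at zero goes beyond the text. The full protocol or a health economic plan may cost it. What stands is narrower: the article does more than stay silent, because it gives a numerator and a data source, and delivery cost is in neither as worded.

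**The payer view rightly leaves out what the insurer does not pay.** This stands. The payer numerator is restricted explicitly to reimbursed costs, and adding staff, peer and website costs to it would change the perspective. The point is confined to the societal numerator.

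**The bootstrap may respect centres.** This also stands. A reader might infer that the article plans a bootstrap that ignores clustering, but cluster and two-stage versions are nonparametric too, and the unit of resampling is a detail that an article may leave to the analysis plan. The figures in step 5 are therefore conditional. They also borrow an ICC that was assumed for EPAS.

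**Baseline utility may be adjusted for.** A reader might infer that QALY differences are left unadjusted. The article does not say so. It states that all other outcomes are analysed much like the primary one, whose model includes the baseline value, centre and centre size. Whether this reaches the ICUR is unclear, so it is something to state and not an error.

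**The remedy is unproven.** In part this stands. A simple centre bootstrap under-covers, and the mixed model and the shrinkage-corrected bootstrap were not simulated here.

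**Conclusion.** The cost point holds for the societal perspective. On the article's own definition, incremental cost is understated in the intervention's favour, because delivery resources fall almost wholly on the experimental arm. The direction is clear. The size cannot be computed from the documents, and the euro ranges above rest wholly on assumed inputs.

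The bootstrap point holds only as a missing statement. If patients were resampled as independent and the EPAS ICC of 0.02 applied at 35 per centre, true standard errors would be about 1.30 times those reported and 95% intervals would cover about 87%. If the ICC for costs and QALYs were zero, nothing would be lost.

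Both parts concern a secondary analysis and leave the confirmatory EPAS test untouched. They are worth correcting because the cost-per-QALY objective depends on them, and because staff and peer time is hard to reconstruct afterwards.

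**What to change.** 1. Log session time (study staff and peer tutor) and materials during the trial. Add a per-patient delivery cost to the experimental arm in the societal numerator, and show development cost separately.
2. Keep the payer numerator as defined. Show delivery cost there as a sensitivity analysis, in case the insurer would fund the programme.
3. State an uncertainty method that respects randomisation of 10 centres. This can be a mixed model for costs and QALYs with random centre, adjusted for baseline cost and baseline EQ-5D-5L, or a two-stage bootstrap (centre, then patient) with shrinkage correction. Build the acceptability curve from it. A simple centre bootstrap is not enough with 5 centres per arm.

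The cost is a little logging and some extra analysis work. Intervals will probably be wider, and the ratio less favourable to the intervention.
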